## **1. Abstract**

In order to safely and effectively reopen businesses and universities across the US, institutions will need to develop approaches to rapidly identify COVID-19 cases and manage their spread while balancing program effectiveness, feasibility, costs, and scalability. We will evaluate the implementation of a COVID-19 screening program that coordinates several existing systems at the University of Pennsylvania including saliva-based viral testing. We will pilot this program to a small cohort of the Penn Medicine workforce and then test different approaches to improve program enrollment that utilize opt-in vs. opt-out framing.

## **2. Overall objectives**

The objective of the study is:

To evaluate the implementation of a COVID-19 screening program that uses saliva-based testing and to determine the effect of an opt-out versus an opt-in approach on program enrollment.

## **3. Aims**

### *3.1 Primary outcome*

The percent of those invited who enroll in the program.

### *3.2 Secondary outcomes*

The distribution of participant sociodemographic characteristics (e.g. age, gender, race/ethnicity), the rate of compliance with saliva-based testing.

### *3.3 Exploratory outcomes*

The cost of the program, barriers and facilitators to scalability, and overall program feasibility.

## **4. Background**

The coronavirus disease 2019 (COVID-19) pandemic has resulted in close to 10,000,000 reported cases worldwide, including more than 2,000,000 aggregated reported cases and 120,000 deaths in the United States [1,2]. Initial efforts to address the COVID-19 pandemic were aimed at testing symptomatic individuals, implementing stay-in-place orders, and at increasing hospital capacity to meet surge demands [3]. While we continue to confront the current crisis, we must plan for the future by putting in place tools to enhance our ability to conduct effective screening, containment, and case management.

Widespread COVID-19 testing is needed to safely and effectively reopen schools and businesses across the US. However, currently approved testing options require reagents that are limited in supply, severely hindering scalability [4]. Emerging evidence indicates that saliva testing with

the option of at-home sample collection can accurately identify COVID-19 viral infection [5]. Additional diagnostic testing options will continue to increase patient access. Moreover, this approach provides an option for the easy, safe and convenient collection of samples required for testing without traveling to a doctor's office, hospital, or testing site. Collection by the patient also reduces exposure of health care workers to the virus and preserves limited personal protective equipment [6].

With access to expanded testing, health systems and universities will need to test alternative methods to manage COVID-19 spread while balancing program effectiveness, feasibility, costs, and scalability. Insights from the field of behavioral economics offer promise for designing and sustaining these kinds of policies. Specifically, research has demonstrated that an opt-out framed recruitment strategy compared to a conventional opt-in strategy can improve enrollment and adherence to behavioral interventions [7-10].

For these reasons, we propose to evaluate the implementation of a COVID-19 screening program that uses saliva-based testing and to test approaches to improve program enrollment.

## **5. Study design**

### *5.1 Design*

We will conduct a clinical trial of at least 6 months beginning with approximately 2500 Penn Medicine employees (faculty, staff and trainees) and potentially increasing as the program rolls out more broadly. In the first phase, we will pilot the approach with up to 50 participants to help optimize implementation. In Phase 2, participants will be randomly assigned to receive an opt-in or opt-out framed study recruitment email. Participants randomly assigned to the opt-in arm will be instructed to visit the Way to Health platform to enroll in the study to call a study coordinator. Participants randomized to the opt-out arm will be told that they have been conditionally enrolled in the voluntary research program and will be instructed to visit the Way to Health platform to get started; participants in this group will receive escalating reminders (e.g. reminder emails, phone call) unless they decline to participate.. Across study arms, interested employees will visit the study website to learn more about the study, create an account, complete a screening survey, provide informed consent, and complete an initial demographic and screening survey.

Enrolled participants will complete additional surveys. All enrolled individuals will be asked to complete and drop off a saliva sample for COVID-19 testing every week (Figure 1). This testing frequency interval may change based on public health and university guidance. Individuals with a positive saliva test will be asked to complete a confirmatory test that is approved by the Clinical Laboratory Improvement Amendments (CLIA) and will be encouraged to self-quarantine while they await results. Individuals with a positive confirmatory test result will be connected to occupational medicine for next steps and will need to follow department specific guidelines for returning to work.

[figure not shown]

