## 5.4 Accrual

Potentially eligible employees will be contacted by email and phone to participate in the study and enrolled via the Way to Health Platform.

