## **6. Subject recruitment**

Leadership from the Perelman School of Medicine will provide an initial list of potentially eligible participants who are University of Pennsylvania faculty, staff, or trainees that have returned to campus for work. We will recruit this population through a combination of emails and phone calls.

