## **9. Analysis plan**

We will use an intention-to-treat approach to evaluate the two-arm randomized trial of opt-in vs opt-out framing for recruitment. We will conduct chi-squared tests to compare the proportion of participants that were invited who enrolled in the program. Using a 2:1 allocation favoring the opt-in group, we estimate that about 1200 employees will need to be enrolled to have >90% power to detect a 10 percentage point difference between an enrollment rate of 30% in the opt-in arm and 40% in the opt-out arm. This assumes a 2-sided  $\alpha$  of <0.05 as statistically significant.

To evaluate the impact of opt-in vs opt-out recruitment on the population enrolled, we will compare age, gender, race/ethnicity of participants that enrolled in the program.

To evaluate the feasibility of the program, summary statistics will be used among the observational cohort to evaluate trends of compliance with saliva-based testing, barriers and facilitators to implementation, and costs of the program.

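### The contrast is labelled opt-in versus opt-out framing, but only the opt-out arm is assigned escalating reminders, so a difference can be credited to the package but not to framing alone

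*Protocol*

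**What the plan says.** Section 5.1 defines what is randomised: "participants will be randomly assigned to receive an opt-in or opt-out framed study recruitment email". It then describes each arm.

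- **Opt-in:** "Participants randomly assigned to the opt-in arm will be instructed to visit the Way to Health platform to enroll in the study to call a". The sentence is garbled and ends by naming a coordinator, so it probably means visit the platform or call. No reminder is described.
- **Opt-out:** people are told they are conditionally enrolled and are sent to the same platform. In addition, "participants in this group will receive escalating reminders (e.g. reminder emails, phone call) unless they decline to participate".

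Section 9 says the analysis will "evaluate the two-arm randomized trial of opt-in vs opt-out framing for recruitment", by intention to treat, with chi-squared tests of enrolment among those invited. The Abstract says the study will "test different approaches to improve program enrollment that utilize opt-in vs. opt-out framing". Section 2 is broader; its aim is "to determine the effect of an opt-out versus an opt-in approach on program enrollment". The Background also speaks of recruitment strategies.

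Two other sections describe contact without naming an arm. Section 5.4 says "Potentially eligible employees will be contacted by email and phone to participate in the study", and section 6 says "We will recruit this population through a combination of emails and phone calls". Neither gives a reminder schedule.

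The primary outcome (section 3.1) is the percentage of invitees who enroll. Section 8.1 ties enrolment to the 4 weeks after invitation. No third arm, factorial element or equal-contact rule appears.

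**The concern.** As described in section 5.1, the arms differ in two ways: the wording of the offer, and the number and channel of contacts after it. Reminders sent within the 4-week window act directly on the primary outcome, and they may raise enrolment under either wording. If the result is reported in the terms of section 9, an effect that may come partly or wholly from follow-up will be credited to framing.

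This matters for use of the result. The Abstract and Background set the work in the context of institutions balancing effectiveness, feasibility, cost and scalability. Changing the wording of an email costs little, while escalating follow-up with phone calls needs staff. A reader who takes the result as a framing effect might change the wording and leave out the calls.

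No analysis plan can separate the two components at 4 weeks once the arms have been run this way. The contrast therefore has to be defined in the protocol before Phase 2 randomisation.

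**Working it through.** **1. What the two arms identify.** Write p(wording, contact) for the 4-week enrolment probability. If section 5.1 is followed literally, the expected difference is

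D = p(out, reminders) − p(in, none)
 = [p(out, none) − p(in, none)] + [p(out, reminders) − p(out, none)]
 = framing effect + reminder effect under opt-out wording.

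The trial observes only p(out, reminders) and p(in, none) at 4 weeks. D is estimated without bias because of randomisation. Its two parts are not identified, because p(out, none) is not observed at 4 weeks. It is observed only up to the first reminder.

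**2. The plan's own power figure.** Inputs from section 9: 30% opt-in, 40% opt-out, 2:1 favouring opt-in, about 1200 people, two-sided 0.05. I take the 1200 as people randomised, giving 800 and 400.

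- Pooled rate = (800 × 0.30 + 400 × 0.40)/1200 = 0.3333
- SE under the null = √[0.3333 × 0.6667 × (1/800 + 1/400)] = 0.02887
- SE under the alternative = √[0.21/800 + 0.24/400] = 0.02937
- Power = Φ[(0.10 − 1.96 × 0.02887)/0.02937] = Φ(1.48) = 93.0%

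With a continuity correction it is 92.1%. The stated figure of more than 90% reproduces, so no number in the plan is wrong.

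**3. Illustration of the attribution problem.** Assume framing has no effect and reminders alone add d points to 30%. The documents give no value for d. For d = 5 points:

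- Pooled rate = (240 + 140)/1200 = 0.3167; SE under the null = 0.02849
- SE under the alternative = √[0.21/800 + 0.2275/400] = 0.02883
- P(significant) = Φ[(0.05 − 1.96 × 0.02849)/0.02883] = Φ(−0.20) = 42%

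| Assumed reminder effect d | P(significant), N = 1200 |
|---|---|
| 2 points | 11% |
| 3 points | 19% |
| 5 points | 42% |
| 7 points | 68% |
| 8 points | 79% |
| 10 points | 93% |

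If everyone outside the pilot were randomised (2500 − 50 = 2450, my assumption and not a figure in the protocol), the values for 5 and 10 points would be 71% and 99.8%.

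**4. The contact passages side by side.** Section 5.1 gives reminder emails and a call to the opt-out arm. Sections 5.4 and 6 describe email and phone contact for the recruited population. If these are summaries across both arms, all three can be true and the opt-in arm gets no reminders. If they apply within each arm, opt-in invitees may be phoned and the contact gap is smaller. The text does not settle which reading applies.

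**The case against.** The strongest reply is that the trial compares two recruitment strategies. Section 2 and the Background use broad terms, and even the Abstract speaks of approaches that use framing. Everyone must actively consent, so nobody is enrolled by doing nothing. Follow-up until the person declines can be seen as what gives conditional enrolment practical meaning. On that reading the reminders belong to the opt-out intervention, and the randomised intention-to-treat comparison answers the question. This stands for the package. It does not cover sections 5.1 and 9, which name a framed email, or framing, as what is compared.

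Three stronger readings are tempting, and the documents do not support them.

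- **That the primary comparison is biased or invalid.** It is valid for the package. Only attribution to framing alone fails.
- **That the percentages in the illustration show inflated type I error.** They are ordinary power for an assumed real difference between the arms. If the two arms' enrolment probabilities were equal, the test would keep its 5% level.
- **That sections 5.4 and 6 contradict section 5.1, or promise phone contact to each arm.** They are general statements that name no arm. They leave opt-in follow-up unclear, which is a lesser fault.

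**Conclusion.** The point holds as one of definition and interpretation. As written, the protocol labels as framing a contrast that also includes escalating reminders in one arm. A positive result would support opt-out framing plus reminders over opt-in recruitment, and would say nothing separate about framing.

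The size of the possible misattribution cannot be derived from the documents, because the planned 10 points are not split between the two components. At one extreme, reminders account for the whole difference, and a result reported as a framing effect would be significant with 93% probability at N = 1200. At the other, they add nothing and the label does no harm. This rests on reading section 5.1 literally, with no reminders for opt-in. If opt-in invitees are also followed up by phone, the contact gap narrows but remains undefined.

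**What to change.** 1. In sections 5.1 and 9, define the contrast as opt-out framing plus escalating reminders versus opt-in recruitment, and limit the conclusion to that package.
2. State in section 5.1 what follow-up, if any, the opt-in arm receives. Align sections 5.4 and 6 with it and repair the garbled opt-in sentence.
3. Add a secondary comparison of enrolment by arm up to the date of the first scheduled reminder, with the same cut-off after invitation in both arms, using dated enrolment records. Label it as supportive evidence on framing. It may cover only part of the 4-week window, so a null result there would not show that framing has no effect.

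The cost is a narrower conclusion, some rewording and one extra table. The primary test and sample size do not change.

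Giving both arms the same reminder schedule is an option only if the sponsor wants to test wording alone. It changes the intervention, needs staff time for opt-in calls and may shrink the planned difference. By the formula above with opt-in at 30%, a framing effect of 7 points would have 68% power at N = 1200 and need about 2138 people for 90%. An effect of 5 points would have 42% power and need about 4133.

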## 5.2 Study duration

The study is expected to begin in July 2020 and participants will continue in the study for 6 months.

## 5.3 Target population

The study sample will be drawn from University of Pennsylvania staff, faculty, and trainees that have returned to work on campus who have been identified by leadership at the Perelman School of Medicine.

## 5.4 Accrual

Potentially eligible employees will be contacted by email and phone to participate in the study and enrolled via the Way to Health Platform.

## 5.5 Key inclusion criteria

To be eligible patients must:

- 1) Be 18 years or older
- 2) Be University of Pennsylvania staff, faculty or trainee
- 3) Have a phone or device capable of receiving text messages
- 4) Willing to participate in the study for 6 months

## 5.6 Key exclusion criteria

Participants will not be eligible if they identify any reason they are unable to participate in the study.

## **6. Subject recruitment**

Leadership from the Perelman School of Medicine will provide an initial list of potentially eligible participants who are University of Pennsylvania faculty, staff, or trainees that have returned to campus for work. We will recruit this population through a combination of emails and phone calls.

## **7. Subject compensation**

No compensation will be offered for this study.

## **8. Study procedures**

### *8.1 Consent*

Informed consent will be obtained electronically through the Way to Health study website since these participants will not be seen in-person. Participants will be able to read through the informed consent and a member of the research team will be available for questions. Once signed, participants will be able to access and print a copy of the combined informed consent/HIPAA form from the Way to Health online platform. Participants will be instructed that they may reach out to the study team with questions and that, since participation is voluntary, they are able to drop out of the study at any time, and that the decision to enroll or not to enroll will have no impact on their employment status at Penn. Enrollment in the study will be defined as a 4 week window after invitation to join.

### *8.2 Procedures*

Participants will be enrolled in the study using the Way to Health platform and asked to complete an initial screening and demographic questionnaire to assess eligibility. If eligible, participants will then complete an informed consent and HIPAA authorization form. Participants will pick up their test kits and drop off their samples at a designated Penn Medicine location. Participants will be instructed to not eat or drink within 30 minutes of providing their saliva sample at the lab. They will provide a sample of at least 1mL into a 50mL test tube and drop off the sample with designated lab staff. Data on symptoms will be obtained from the mandatory Penn Medicine symptom monitoring program (PennOpen Pass). If a participant remains symptom free, they will complete a saliva-based screening test. Results will be shared with the study team using LabVantage, a Laboratory Information Management System, and the study team will communicate these results to the study participant. If the results of the saliva screening test are negative, data will continue to be collected on symptoms and timing of the next saliva test will be given.

If results of the saliva screening test are positive, participants will be referred to the PennOpen Pass Call Center where they will receive guidance on how to obtain a CLIA approved test to confirm diagnosis of COVID-19. They may also be directed to contact tracing, advised to enter self-quarantine. Upon receipt of a positive result, they will be given next steps for returning to work. If results of the CLIA approved test are negative, participants will re-enter daily symptom monitoring and timing of the next saliva test will be given.

The COVID-19 screening test was developed by University of Pennsylvania faculty and staff on the Rapid Assay Task Force. The task force was assembled under the direction of [name], Chief Scientific Officer and Vice Dean at the Perelman School of Medicine and is led by [name], Professor and Chair of the Department of Microbiology. The saliva-based test is conducted using a highly sensitive reverse-transcription loop-mediated isothermal amplification (RT-LAMP) assay compatible with reagents developed at the University of Pennsylvania to detect SARS-CoV-2 viral RNA. LAMP is a method of isothermal DNA replication that utilizes, in an accelerated format, DNA oligos that hybridize with different regions of the target molecule. Utilizing a strand displacing polymerase and loops formed during this reaction, a fast amplification reaction can occur upon proper oligo binding to the desired target. Such reactions are capable of generating microgram quantities of DNA in a very short period of time at a single reaction temperature. Furthermore, although the strand-displacing polymerase has reverse transcriptase activity, a reverse transcriptase can be included to improve sensitivity within the reaction when detecting an RNA target (RT-LAMP). The saliva test developed by the University of Pennsylvania uses SARS-CoV-2 specific primer sets, designed uniquely to detect SARS-CoV-2 RNA. The protocol is simple, inexpensive, and rapid. Results are typically available in about one hour. Positive samples are called by comparison to positive and negative controls; reactions displaying a color shift indicate that the target sequence is present. Positive results are indicative of the presence of SARS-CoV-2-RNA but must be confirmed by a CLIA approved test. Existing reports suggest that assays based upon these protocols allow for a sensitivity down to at least 1 genome per microliter when starting with 0.5 ml of saliva [11].

Quality control (QC) checks will occur at multiple points in this protocol:

1. Sample QC – Verify all samples are contained within the appropriate container, are labeled with two unique identifiers, and that samples have been stored appropriately prior to arrival in the laboratory.
2. Verify that all required materials are available in the necessary quantities prior to protocol initiation.
3. Ensure that all reagents used are within the expiration date and that all reagents used have been properly validated.
4. Prior to starting the procedure, ensure all required tubes have been properly labeled.

5. A positive control QC step, consisting of LAMP reactions spiked with synthetic SARS-CoV-2 RNA, is performed to ensure that the LAMP reaction worked as expected.
6. A negative control QC step, consisting of LAMP reactions spiked with human total RNA, is performed to ensure that no contamination of LAMP reagents has occurred.

## **9. Analysis plan**

We will use an intention-to-treat approach to evaluate the two-arm randomized trial of opt-in vs opt-out framing for recruitment. We will conduct chi-squared tests to compare the proportion of participants that were invited who enrolled in the program. Using a 2:1 allocation favoring the opt-in group, we estimate that about 1200 employees will need to be enrolled to have >90% power to detect a 10 percentage point difference between an enrollment rate of 30% in the opt-in arm and 40% in the opt-out arm. This assumes a 2-sided  $\alpha$  of <0.05 as statistically significant.

To evaluate the impact of opt-in vs opt-out recruitment on the population enrolled, we will compare age, gender, race/ethnicity of participants that enrolled in the program.

To evaluate the feasibility of the program, summary statistics will be used among the observational cohort to evaluate trends of compliance with saliva-based testing, barriers and facilitators to implementation, and costs of the program.

## **11. Human research protection**

### *11.1 Data confidentiality*

Paper-based records will be kept in a secure location and only be accessible to personnel involved in the study. Computer-based files will only be made available to personnel involved in the study through the use of access privileges and passwords. Wherever feasible, identifiers will be removed from study-related information. Lab-based data and test kits will use a barcode linked to the participant study number. In the event of a positive test result, we will use this information to notify the participant. Lab staff may be privy to participant identity but have been trained to maintain confidentiality. Precautions are in place to ensure the data are secure by using passwords and encryption, because the research involves web-based surveys.

